### 2.3. Eligibility Criteria

Participants for this study will be recreational adult dancers aged ≥ 18 years with a minimum of 6 months prior recreational dance experience at community dance schools. Eligible participants must demonstrate capacity for sustained moderate-intensity movement (60 min sessions) and good health with no severe musculoskeletal injuries within the past 2 weeks or intense medical conditions preventing coordinated group movement. Participants must commit to attending at least 70% of sessions (minimum 8 of 12 weeks) and baseline and post-intervention assessments, and be fluent in Greek language (written/verbal).

Exclusion criteria include: (1) active engagement in concurrent mindfulness-based or somatic-movement practices (yoga, Pilates, tai-chi, MBSR programs, etc.), which share theoretical overlap with the intervention’s mindfulness and embodied awareness components and could confound results; (2) severe psychiatric symptomatology requiring clinical psychiatric intervention (hospitalization, crisis stabilization, active suicidality). However, individuals with stable, treated psychiatric conditions are eligible, provided they have been stable on their current medication for a minimum of 6 months and have medical clearance from their treating clinician confirming appropriateness for moderate-intensity physical activity; (3) active substance abuse or dependence (current or within the past 12 months); (4) significant uncorrected hearing or vision impairment affecting the ability to participate in group dance and receive verbal or visual instructions; (5) current pregnancy; (6) acute physical contraindication to movement, including intense musculoskeletal injury occurring within 2 weeks prior to enrollment, severe infection, or uncontrolled cardiovascular event.

Individuals with injuries, mild to moderate, well-controlled chronic medical conditions (e.g., diabetes, hypertension, asthma, arthritis) or stable chronic psychological conditions are not exclusionary if participants provide written medical clearance from their treating physician/clinician confirming capacity for sustained moderate-intensity movement (90–100 min sessions) and documenting any activity modifications required. Severe or poorly controlled chronic conditions are exclusionary and require individual assessment by the principal investigator in consultation with the participant’s clinician.

During preliminary telephone or in-person screening, trained site coordinators conduct structured interviews assessing adherence to inclusion and exclusion criteria. Prospective participants receive a comprehensive eligibility information sheet listing all criteria in accessible language and are invited to self-identify any exclusions or concerns. Those meeting preliminary eligibility criteria (age ≥ 18, minimum 6 months recreational dance experience, availability to attend ≥70% of sessions, Greek language fluency) proceed to formal baseline assessment. Site coordinators maintain a screening log documenting all preliminary screenings, including numbers screened, numbers excluded at each stage, and reasons for exclusion, to enable identification of potential selection bias.

### 2.4. Sample Size and Recruitment

To determine the appropriate sample size for this study, a power analysis was conducted using GPower 3.1 software [32]. The analysis was based on a repeated-measures design with two groups (experimental and control), with measurements taken at baseline and post-intervention. The following parameters were used: Effect Size (Cohen’s d) = 0.50 (medium effect); Alpha Level (α) = 0.05 (5% significance threshold); Power (1 − β) = 0.80 (80% probability of detecting a true effect); two measurement time points (pre- and post-intervention); and two groups (experimental and control). According to the power analysis, the minimum sample size required to achieve sufficient statistical power is 114 participants, with 38 participants in the control group and 76 in the experimental group.

Participants will be informed about the study through targeted outreach at private recreational dance schools in four cities (Larissa, Trikala, Karditsa, Kalampaka) within the Thessaly region, Greece, with an estimated 1–2 participating schools across these cities. Recruitment methods include flyers, posters, verbal announcements during dance classes, and direct recruitment by dance school directors. Recruitment occurs over an anticipated 1–2 month period, with baseline assessments completed by the end of Month 2. During initial contact, prospective participants receive a participant information sheet detailing study aims, procedures, risks, benefits, confidentiality protections, and withdrawal rights. The information sheet describes the study as “a 12-week integrated modern dance program” without mentioning mindfulness components, to minimize selection bias toward mindfulness-seeking participants. Individuals expressing interest undergo preliminary telephone or in-person screening with a trained site coordinator to assess adherence to inclusion and exclusion criteria (Section 2.3). Those meeting preliminary eligibility criteria are informed of the next steps. Individuals with intense mental health distress or active engagement in concurrent mindfulness-based interventions are offered future participation following symptom resolution or completion of conflicting interventions, rather than immediate exclusion.

Participants proceed to formal baseline assessment (T0), which includes informed consent and administration of quantitative outcome measures (SWLS, DASS-21, MAAS, SHS, LIS; approximately 20–30 min). After completion of baseline assessment (T0), eligible participants are randomly allocated 2:1 (intervention: control) using computer-generated randomization with allocation concealment (administered by an independent data manager not involved in recruitment or assessment). Randomization is conducted via a secure, password-protected electronic system accessible only to the data manager, ensuring that recruitment staff and outcome assessors remain blind to allocation. Following randomization, intervention group participants receive full disclosure of the 12-week dance-mindfulness protocol and provide additional written informed consent confirming understanding of the intervention and commitment to attending the sessions.

Control group participants receive written guidelines regarding their usual recreational dance activities during the 12–week study period, including instructions to exclude concurrent mind–body practices (yoga, Pilates, tai-chi, MBSR programs, etc.). Control group participants are informed that they will have access to the full 12-week dance-mindfulness program at no cost after post-intervention assessment (T2, Week 12), providing equitable delayed intervention access.

Site coordinators maintain a screening log documenting all preliminary screening contacts, including date of screening, recruitment source, preliminary eligibility status (age, dance experience, attendance availability, language fluency), exclusion criteria met (if applicable, specifying which criterion 1–6), clearance documentation status, and disposition (enrolled in baseline assessment, not meeting criteria, awaiting clearance). This log enables complete CONSORT [31] flowchart documentation and allows identification of potential selection bias or recruitment barriers. In the event that randomized participants withdraw or fail to meet attendance criteria (≤70% of sessions), they are retained in all analyses using intention-to-treat methodology. Missing outcome data will be addressed through multiple imputation or last-observation-carried-forward approaches, as appropriate based on data missingness patterns. Replacement participants are not recruited mid-trial, as this would create methodological complications (unbalanced final sample size, potential confounding from replacement timing differences). Final sample size analyzed may differ from target sample size and will be fully documented in the CONSORT compliant participant flowchart, which will be generated upon study completion detailing actual enrollment, randomization, and attrition data by group and reason for withdrawal.

All participants provide written informed consent prior to baseline enrollment. Personal data are handled in strict compliance with the General Data Protection Regulation. All participant identifiers are replaced with unique numeric codes; codebooks linking codes to identifying information are encrypted and stored separately from all research data, accessible only to the principal investigator. Paper materials are stored in locked filing cabinets in restricted-access laboratory space; digital data are stored on secure, password-protected institutional servers with automated daily backups. Data are retained for five years following study completion; paper documents are shredded, and digital data securely deleted thereafter, in accordance with institutional policies and GDPR regulations.

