### 2.7. Data Collection and Analysis

Self-report questionnaires (SWLS, DASS-21, MAAS, SHS, LIS) are administered on paper at baseline (T0) and post-intervention (T2) by trained site coordinators in quiet studio environments (~20–30 min per assessment). Questionnaires are entered into a secure electronic database with double-entry verification.

Demographic and baseline characteristics are summarized using descriptive statistics (means, standard deviations, medians, frequencies, percentages). Shapiro–Wilk tests and visual inspection (Q-Q plots, histograms) assess normality for all primary outcome variables. Between-group demographic comparisons use independent-samples *t*-tests (continuous) and chi-square tests (categorical). Internal consistency is assessed using Cronbach’s alpha (α ≥ 0.70); test–retest reliability via intraclass correlation coefficients (ICC ≥ 0.70) in the control group.

If normality is met (Shapiro–Wilk *p* > 0.05), a 2 (Group) × 2 (Time) mixed-model repeated-measures ANOVA is conducted on each primary outcome, with Bonferroni-corrected α = 0.01 to control Type I error. Alternative testing via MANOVA (Wilks’ Lambda, α = 0.05) proceeds to univariate ANOVAs if significant. ANCOVA with T0 baseline covariates is conducted with Levene’s test assessing homogeneity of variance; if violated (*p* < 0.05). Effect sizes and 95% confidence intervals are reported.

If normality is violated (Shapiro–Wilk *p* < 0.05), non-parametric tests will be used: Friedman’s test (within-group time effects), Mann–Whitney U (between-group comparisons), Wilcoxon signed-rank test (within-group pre–post). Post hoc pairwise comparisons use Bonferroni-corrected alpha. Pearson correlations (Bonferroni-corrected) for normally distributed variables; Spearman’s rank-order correlations for non-normal variables. Correlations ≥ |0.30| are highlighted. Quantitative analyses use IBM SPSS v. 28; results are reported per CONSORT guidelines [31] with summary statistics, 95% confidence intervals, and effect sizes. Significance level: α = 0.05 (two-tailed) unless otherwise specified (Bonferroni-corrected α = 0.01).

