Although the present protocol is grounded in Harrison et al.’s [7] theoretical framework regarding mindfulness-acceptance-commitment interventions in dancers, it differs in three dimensions. The population differs in that Harrison et al. examined 16 professional ballet dancers with limited time for mindfulness practice, whereas the present protocol targets recreational dancers who are motivated by intrinsic satisfaction rather than professional demands. The intervention structure also differs, replacing six standalone 30 min sessions with 12 sessions of 90–100 min with mindfulness embedded directly within structured choreography rather than as parallel practice. The theoretical framework extends substantially by integrating polyvagal theory and motor learning science directly into pedagogical structure and using a broad spectrum of psychological and qualitative measures, and phenomenological interviews for multidimensional assessment, whereas Harrison et al. [7] implemented only the MAC model with athlete-specific measures. Where Harrison et al. [7] found no statistically significant differences attributed to small sample size and brief duration, the present protocol addresses these limitations with 114 participants and doubles the intervention length, with embedded integration expected to enhance adherence and efficacy.

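### The stated minimum of 114 for 80% power makes no allowance for missing Week 12 data, yet 114 is also the only trial size given and withdrawals are not replaced

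*Protocol article*

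**What the plan says.** Section 2.4 (Sample Size and Recruitment) describes a power analysis for two groups measured at baseline and post-intervention. It uses Cohen's d of 0.50, alpha of 0.05 and power of 0.80, and concludes that "the minimum sample size required to achieve sufficient statistical power is 114 participants, with 38 participants in the control group"; the remaining 76 go to the intervention arm. No loss rate and no pre-post correlation are listed.

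The same section says what happens to participants who withdraw or attend too little. They stay in the intention-to-treat analysis, and missing outcomes are handled by multiple imputation or last observation carried forward. It adds that "Replacement participants are not recruited mid-trial" and that "Final sample size analyzed may differ from target sample size".

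Section 5 (Discussion) compares the trial with an earlier study of 16 professional dancers whose null result was put down to small sample and short duration. It says that "the present protocol addresses these limitations with 114 participants" and a longer intervention.

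Sections 2.1, 2.5 and 3.2 place the questionnaires at T0 and T2 only.

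**The concern.** A figure described as the minimum for 80% power is also the only size given for the trial. The protocol has a rule for withdrawals but adds no margin for them and will not replace them. With questionnaires only at T0 and T2, a participant who misses T2 has no other post-baseline score. Imputing T2 from T0 keeps that person's record in the analysis but does not recover the missing information. Carrying the last observation forward sets the person's change to zero.

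If T2 data are lost in more than trivial numbers, the trial has less power on the calculation's own basis than section 2.4 states. A reader of a null result would take the 80% at face value, the more so because the Discussion offers 114 as the answer to an earlier study's small sample.

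**Working it through.** **Inputs from the protocol.** d = 0.50, alpha = 0.05 (sidedness not given in section 2.4), power 0.80 and N = 114 as 38 + 76 (section 2.4); 2:1 allocation (section 2.1). **Assumed here:** T2 losses of 10%, 15% and 20%, equal in both arms, because the protocol gives no rate.

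**Step 1: reproduce 114.** For two means with allocation ratio k = 2, on the standardised scale:

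n(control) = (1 + 1/k) × (z(1−α) + z(1−β))² / d²

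- One-sided 0.05: 1.5 × (1.645 + 0.842)² / 0.25 = 37.1, rounded up to 38. This gives 38 + 76 = 114, an exact match, and a noncentral-t calculation gives the same.
- Two-sided 0.05: 1.5 × (1.960 + 0.842)² / 0.25 = 47.1, rounded up to 48. This gives 48 + 96 = 144, which does not match.

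A two-sided change-score test also gives 114 if a pre-post correlation of 0.6 is assumed, but the protocol states no correlation. Either way, 114 is a figure with no dropout allowance.

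**Step 2: slack at 38/76.** Power is the probability that a noncentral t, with n₁ + n₂ − 2 degrees of freedom and noncentrality d × √(n₁n₂/(n₁+n₂)), exceeds the critical value. At 38/76 the noncentrality is 0.50 × √(38 × 76/114) = 2.517, the one-sided critical value is 1.659, and power is 0.804.

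Small losses on the same basis:

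| Control / experimental with T2 | Power |
|---|---|
| 38 / 76 | 0.804 |
| 38 / 75 | 0.803 |
| 38 / 74 | 0.801 |
| 38 / 73 | 0.799 |
| 37 / 76 | 0.798 |

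**Step 3: proportional loss.** Numbers with T2 data are 38 × (1 − loss) and 76 × (1 − loss), rounded to whole people:

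| Assumed T2 loss | With T2 data | Noncentrality | Power, one-sided 0.05 |
|---|---|---|---|
| 0% | 38 / 76 | 2.517 | 0.804 |
| 10% | 34 / 68 | 2.380 | 0.764 |
| 15% | 32 / 65 | 2.315 | 0.743 |
| 20% | 30 / 61 | 2.242 | 0.719 |

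The part due to attrition is therefore 4.0, 6.1 and 8.5 percentage points.

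**Step 4: does the direction depend on the basis?** On the two-sided 0.05 change-score basis with an assumed r = 0.6, where the standardised effect is d/√(2(1 − r)), power at 38/76 is 0.797. It falls to 0.750, 0.727 and 0.698 at the same three losses. The fall is of similar size.

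**The case against.** Several points on the other side stand.

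- **Withdrawals are provided for, not forecast.** The rule in section 2.4 is conditional and carries no rate. Sections 2.3 and 3.5 also work to limit loss: participants commit to attendance and to both assessments, missed sessions are followed up within 48 hours, and make-up sessions and practical support are offered. These measures may reduce loss but do not replace an allowance for it.
- **That 114 is the enrolment number is an inference.** Section 2.4 calls it a minimum and mentions a target without giving one. Only the Discussion sentence ties 114 to the trial as run. No larger number appears, so the inference is reasonable, but the protocol should settle it.
- **A reader might infer that any loss breaks the 80% claim.** It does not in any useful sense: one or two losses leave power at 0.80 to rounding.
- **A reader might infer that 80% is out of reach once data are lost.** The documents do not support that. Section 2.7 plans a Group × Time ANOVA and an ANCOVA with T0 covariates, which can use the baseline score. At 32/65, d = 0.50 and two-sided 0.05, ANCOVA power is 0.75, 0.82 and 0.89 for assumed pre-post correlations of 0.5, 0.6 and 0.7. Change-score power is 0.63, 0.73 and 0.84. With a correlation of about 0.6 or more, ANCOVA would still exceed 80% after 15% loss. The protocol states no correlation, so this can be neither claimed nor excluded.
- **A reader might attach the much lower figures to attrition.** Section 2.7 sets "Significance level: α = 0.05 (two-tailed) unless otherwise specified (Bonferroni-corrected α = 0.01"). At 38/76 with no loss, the two-sample test has power of 0.70 at two-sided 0.05 and 0.46 at two-sided 0.01. Those drops come from sidedness and the Bonferroni correction, which is a separate problem.
- **A reader might add a further cut for low attenders diluting the effect.** Section 2.4 labels d = 0.50 only as a medium effect and does not say that it assumes full adherence, so the documents give no basis for a dilution figure.

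**Conclusion.** The concern holds in limited form. The power statement in section 2.4 has no allowance for missing T2 data. The same 114 is the only trial size the protocol gives, and losses are not replaced. The 80% applies to complete T2 data on the calculation's own basis.

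On that basis the shortfall is modest: about 0.76, 0.74 and 0.72 in place of 0.80 at 10%, 15% and 20% loss. This rests on three assumptions: the loss rates, equal loss in both arms, and the one-sided two-sample test that reproduces 114. Power under the planned analysis could be higher or lower, depending on the unstated pre-post correlation and on which alpha applies.

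The documents do not support a stronger conclusion that the trial cannot reach 80%, or that its size is no improvement on the earlier study. That study had 16 dancers, and 114 remains about seven times as large (114/16 = 7.1).

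**What to change.** In section 2.4, state whether 114 is the number randomised or the number with T2 data. If it is the number randomised, give an assumed T2 loss with its reason. At 15%, for example, 38 × 0.85 = 32.3 and 76 × 0.85 = 64.6, so about 32 + 65 would have T2 data. Then restate the power for that number using the test, sidedness, alpha and pre-post correlation of the planned analysis, in place of the unqualified 80%.

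In section 5, describe 114 as the number enrolled. The comparison with the earlier study need not be dropped.

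The cost is one recalculated statement in section 2.4 and a qualifier in section 5. No extra enrolment is required, though the stated power may become less favourable. Because the restated figure must use the planned alpha and sidedness, it should be prepared together with the reconciliation of sections 2.4 and 2.7 on those points. An attrition allowance alone would not resolve that mismatch.

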## 2. Experimental Design

### 2.1. Trial Design

This study has been prospectively registered on ClinicalTrials.gov (NCT07262177; brief title: Dance-Mindfulness Intervention for Well-Being in Recreational Adults-DanceMind) and approved by the institutional Research Ethics Committee (IEC, DPESS, UTH 4-2/2.4.2025; Supplementary File S8 [27]). The protocol follows SPIRIT [28,29], TIDieR [30], and CONSORT standards [31].

This is a two-parallel group randomized controlled trial (RCT). The intervention group receives a 12-week integrated dance-mindfulness protocol grounded in polyvagal theory, motor learning science, and embodied phenomenology. The control group continues regular recreational dance activities without mindfulness or somatic-reflective components. Participants are randomly allocated 2:1 (intervention: control) using computer-generated randomization with allocation concealment.

Quantitative assessments occur at baseline (T0) and post-intervention (T2 Week 12). Qualitative data collection occurs at mid-intervention (T1 Week 8) and post-intervention (T2 Week 12). This mixed-methods design permits concurrent testing of quantitative psychological outcomes (life satisfaction, subjective happiness, psychological distress, mindful attention, leisure involvement) and qualitative embodied experiences (somatic awareness, nervous system resilience, technical confidence, creative expression, relational belonging, meaning-making).

All procedures follow ethical principles outlined in the Declaration of Helsinki. Written informed consent is obtained prior to enrollment. Participants have the right to withdraw at any time without consequence. Personal data are stored securely in encrypted databases. Each participant receives a unique study code; identifying information is separated from research data. All facilitators hold CPR/First Aid certification and mindfulness training. Session checklists document adverse events. If a participant reports intense psychological distress, the study is suspended for that individual with clinical referral provided. Facilitators are trained to recognize signs of emotional dysregulation and provide immediate basic containment (quiet space, grounding breath), without attempting psychological exploration. Control group participants receive delayed access to the intervention after post-intervention assessment (Supplementary Files S1–S8 [27]).

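### N = 114 is sized for 80% power at alpha 0.05, but each of five primary outcomes is tested two-sided at 0.01, where power for d = 0.5 is about 46% if the pre-post correlation is 0.5

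*Protocol article*

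**What the plan says.** Section 2.4 describes the calculation in these terms: "The analysis was based on a repeated-measures design with two groups (experimental and control), with measurements taken at baseline and post-intervention". Its inputs are an effect given as "Effect Size (Cohen’s d) = 0.50 (medium effect"), a level given as "Alpha Level (α) = 0.05 (5% significance threshold") and a target given as "Power (1 − β) = 0.80 (80% probability of detecting a true effect"). The result, presented as a lower bound, reads: "sample size required to achieve sufficient statistical power is 114 participants, with 38 participants in the control group and 76 in the experimental group". Section 2.1 fixes the allocation: "Participants are randomly allocated 2:1 (intervention: control"). Section 2.4 does not say whether the test is one- or two-sided, what pre-post correlation was assumed, or whether d is in units of the raw-score or the change-score SD. It adds no margin for dropout, and the same section rules out replacing participants during the trial.

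Section 1.2 names five primary quantitative outcomes. Section 2.7 plans a 2 × 2 mixed ANOVA on each of them at a Bonferroni-corrected 0.01, and closes with: "Significance level: α = 0.05 (two-tailed) unless otherwise specified (Bonferroni-corrected α = 0.01"). It also names a MANOVA at 0.05 as an alternative route, and an ANCOVA with baseline covariates.

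The Discussion relies on the figure. Referring to an earlier study's small sample and short duration, it says that "the present protocol addresses these limitations with 114 participants" and a longer intervention.

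**The concern.** The significance level used for sizing is five times the level at which each primary outcome will be judged. A power of 80% at 0.05 is not 80% at 0.01, and both statements stand in the same article, so this is not a detail left to a separate analysis plan.

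The calculation also cannot be checked as described. A repeated-measures calculation needs a pre-post correlation, and none is given. The stated split of 38 and 76 coincides with what a one-sided two-sample t-test returns, whereas the planned tests are two-sided.

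Interpretation is what is at stake. If a primary outcome misses 0.01, readers told that the trial had 80% power will take this as evidence against a medium effect. Depending on the correlation, the test may have had a much lower chance of finding one.

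**Working it through.** **Inputs.** From section 2.4: d = 0.50, alpha 0.05, power 0.80, 38 control and 76 intervention. From section 2.7: two-sided tests at 0.05/5 = 0.01 per primary outcome. Assumed, because the article gives no value: pre-post correlation ρ from 0.3 to 0.8, and attrition of 15%.

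**Formula.** Power is the tail area of a noncentral t with n₁ + n₂ − 2 = 112 degrees of freedom and noncentrality δ = d_eff × √(n₁n₂/(n₁ + n₂)), beyond the critical t. For 38 and 76, √(38 × 76/114) = 5.033. With d_eff = 0.50, δ = 2.517.

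**Step 1: reproduce 114.** One-sided 0.05 (critical t 1.659) gives 80.4% with 38/76 and 79.5% with 37/74. At 2:1, 38/76 is therefore exactly the smallest size that reaches 80%. That this was the method used is an inference from the match.

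Other routes can also give about 114, but only with an unstated correlation:
- The between-group effect of a repeated-measures ANOVA, with f = 0.25, two-sided 0.05 and λ = f² × N × 2/(1 + ρ), needs N = 97 at ρ = 0.5 and N = 114 at ρ = 0.77 to 0.78.
- The Group × Time test at two-sided 0.05, with d on the raw-score SD, reaches 80% with 38/76 at ρ of about 0.60 (step 3).
- Entering f = 0.25 directly as the interaction effect, λ = f² × N × 2/(1 − ρ), gives 65, 46 and 34 at ρ = 0, 0.3 and 0.5, so not 114.

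**Step 2: the same N at the planned level, d_eff = 0.50.** This covers a comparison of post-scores, a change-score test at ρ = 0.5, or d defined on the change-score SD.

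| Test | Critical t | Power, 38/76 | Size for 80% | Detectable d at 80% |
|---|---|---|---|---|
| One-sided 0.05 | 1.659 | 80.4% | 38/76 = 114 | 0.50 |
| Two-sided 0.05 | 1.981 | 70.4% | 48/96 = 144 | 0.56 |
| Two-sided 0.01 | 2.620 | 46.2% | 72/144 = 216 | 0.69 |

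**Step 3: dependence on ρ, with d = 0.50 on the raw-score SD.** The Group × Time test is a t-test on change scores, with d_eff = 0.50/√(2(1 − ρ)). For ANCOVA on baseline, d_eff = 0.50/√(1 − ρ²).

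| ρ | G × T d_eff | G × T, 0.05 | G × T, 0.01 | ANCOVA d_eff | ANCOVA, 0.05 | ANCOVA, 0.01 |
|---|---|---|---|---|---|---|
| 0.3 | 0.423 | 55.9% | 31.5% | 0.524 | 74.4% | 50.9% |
| 0.5 | 0.500 | 70.4% | 46.2% | 0.577 | 82.1% | 61.3% |
| 0.6 | 0.559 | 79.7% | 57.8% | 0.625 | 87.7% | 70.0% |
| 0.7 | 0.645 | 89.6% | 73.4% | 0.700 | 93.7% | 81.5% |
| 0.8 | 0.791 | 97.6% | 91.1% | 0.833 | 98.6% | 94.0% |

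Solving for 80% power gives ρ of about 0.60 (Group × Time) and 0.45 (ANCOVA) at two-sided 0.05, and about 0.74 and 0.69 at two-sided 0.01.

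**Step 4: attrition.** At an assumed 15% loss, 114 × 0.85 ≈ 97, taken as 32/65. If those lost contribute no information, δ = 0.50 × √(32 × 65/97) = 2.315, and power at two-sided 0.01 with d_eff = 0.50 is about 38%.

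**The case against.** The best defence is that the design is repeated measures, so a two-sample calculation understates what 114 can do. This has force. With d on the raw-score SD, 114 gives 80% at two-sided 0.05 from ρ of about 0.60 on change scores and about 0.45 with ANCOVA, and ANCOVA is among the planned analyses. At 0.01, ANCOVA has 81.5% at ρ = 0.7. Section 2.7 also names a MANOVA at 0.05, so 0.01 is not the only testing route.

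Two stronger readings are therefore not supported. A reader might infer from the exact match of 38/76 that 80% power is valid only for a one-sided test. The article never says one-sided, other routes reach 114, and two-sided 0.05 attains 80% at ordinary correlations. A reader might also conclude that the trial simply has 46% power and misses a medium effect more than half the time. That holds for a post-score comparison, for Group × Time at ρ = 0.5, or for d on the change-score SD, but not in general. Nor is the repeated-measures description wrong in itself, since the planned analysis is one. What is missing is the correlation.

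The defence does not remove the mismatch. None of the routes to 114 uses 0.01, the level fixed for the ANOVA on each primary outcome, and no power is stated for the MANOVA. The only nearby figure, an ICC threshold of 0.70 in controls, is a reliability criterion and not a planning assumption. Even at ρ = 0.70 the planned 2 × 2 ANOVA has 73.4% at 0.01.

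**Conclusion.** The stated power does not belong to the planned test. Sizing was at 0.05, with sidedness and correlation unstated, while each of the five primary ANOVAs is judged two-sided at 0.01. Across ρ from 0.3 to 0.7, the Group × Time test at 0.01 stays below the claimed 80% throughout, and ANCOVA passes it only near the top of that range.

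These figures assume d = 0.50, complete data on 76 and 38, equal variances and, for the correlation-dependent values, d on the raw-score SD. The missing dropout margin is secondary, but it lowers power further under any plausible loss. Type I error and the validity of the randomisation are not affected. The defect lies in what the trial claims to be able to detect, and in how the Discussion presents 114 as an answer to a small sample.

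**What to change.** Keep N = 114 and rewrite the sample-size paragraph in section 2.4 so that it:
- names the test being powered (Group × Time or baseline-adjusted ANCOVA), two-sided at 0.01;
- says which SD d refers to;
- gives an assumed pre-post correlation with a range, and an assumed attrition rate;
- reports the resulting power, or the detectable d, which is 0.69 at 80% power without baseline adjustment and before attrition;
- no longer claims 80% power on each primary outcome without those conditions.

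The repeated-measures description can stay once the correlation is stated. The Discussion sentence on 114 participants should be qualified to match.

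The cost is one rewritten paragraph, one qualified sentence and a less favourable stated power. Recruitment, outcomes and the analysis are unchanged.
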